## Abstract

**Background:**

Intervention studies testing the efficacy of cardiorespiratory exercise have shown some promise in terms of improving cognitive function in later life. Recent developments suggest that a multi-modal exercise intervention that includes motor as well as physical training and requires sustained attention and concentration, may better elicit the actual potency of exercise to enhance cognitive performance. This study will test the effect of a multi-modal exercise program, for older women, on cognitive and physical functioning.

**Methods/design:**

This randomised controlled trial involves community dwelling women, without cognitive impairment, aged 65–75 years. Participants are randomised to exercise intervention or non-exercise control groups, for 16 weeks. The intervention consists of twice weekly, 60 minute, exercise classes incorporating aerobic, strength, balance, flexibility, co-ordination and agility training. Primary outcomes are measures of cognitive function and secondary outcomes include physical functioning and a neurocognitive biomarker (brain derived neurotrophic factor). Measures are taken at baseline and 16 weeks later and qualitative data related to the experience and acceptability of the program are collected from a sub-sample of the intervention group.

**Discussion:**

If this randomised controlled trial demonstrates that multimodal exercise (that includes motor fitness training) can improve cognitive performance in later life, the benefits will be two-fold. First, an inexpensive, effective strategy will have been developed that could ameliorate the increased prevalence of age-related cognitive impairment predicted to accompany population ageing. Second, more robust evidence will have been provided about the mechanisms that link exercise to cognitive improvement allowing future research to be better focused and potentially more productive.

**Trial registration:**

Australian and New Zealand Clinical Trial Registration Number: ANZCTR12612000451808

## Background

Ageing is associated with decline in cognitive functions that are critical to independence, social engagement, and quality of life. Unchecked, this normal and gradual deterioration can advance to clinical cognitive impairment which, in turn, carries a higher risk for progression to dementia [1-3]. As the proportion of people aged over 65 years continues to expand, it is estimated that, by 2050, dementia could affect some 106.2 million people globally [4]. Age-related cognitive decline affects far more people than dementia [5]; so, there is much to be gained at the economic, social and individual levels if an effective, inexpensive approach to age-related cognitive impairment, can be found.

Exercise training has been identified as a promising countermeasure, to age-related cognitive decline [6]. The search for definitive evidence has seen a trend away from non-experimental and quasi-experimental research toward randomised controlled trials (RCTs). Systematic reviews of this literature suggest that formal exercise training resulting in increased cardiorespiratory fitness can improve cognitive performance in older people [7-9]. However, there is still much to be clarified. While cardiovascular exercise demonstrates a moderate effect on cognition, according to a Cochrane review, there is insufficient evidence that cognitive improvements can be attributed to improved cardiovascular fitness [7]. The suggestion is that other factors may be involved and more recently a number of areas have been identified as important targets for future research. These include the motor aspect of exercise [10,11]; and combined modality exercise interventions to address the limitations of repeatedly evaluating a single component of exercise training in relation to cognition [12]. Accordingly this study will adopt a novel approach by combining key emerging themes from the extant literature [13]. Specifically, this study is a RCT of a multi-modal exercise intervention, based on a broad definition of fitness which includes motor (balance, co-ordination, agility, proprioception, flexibility and reaction time) [12] and physical (cardiovascular and resistance) components.

The mechanisms that underpin exercise-induced cognitive gains are also receiving greater attention. This focus has largely been propelled by evidence that indicates that the brain retains a life-long capacity to change and adapt in response to environmental and experiential stimuli, including exercise training [14]. This capacity, referred to as neuroplasticity, has been demonstrated in exercise trained ageing animals [15-18]; and the prospect of similar possibilities in older humans has attracted significant interest [10,19]. As yet, the mechanisms of human brain plasticity (changes in brain structure and function) and cognitive plasticity (changes in cognitive performance), are poorly understood. There are, however, theoretical indications that these changes may be more likely to occur as a result of interventions that involve novelty and complexity that necessitates mental effort [12,15]; otherwise known as cognitive load [20]. Significantly sustained mental effort is a feature of motor skills acquisition. In addition, there is some evidence, mostly from animal studies, that exercise-induced brain changes may be mediated by neurotrophins (proteins that play a role in neurone development), such as, brain-derived neurotrophic factor (BDNF) [19]. BDNF may play a key role in brain plasticity by regulating the growth, maintenance and survival of neurons in the adult brain. Mixed results from the few human studies indicate that poorly understood gender effects may obscure the interpretation of BDNF levels as a biomarker of cognitive function [21]. Recently, Coelho et al. [22] found higher levels of plasma BDNF in response to an exercise intervention in older women (before 351 ± 68 pg/ml and after 593 ± 79 pg/ml; p < 0.001). Accordingly this study will focus on older women.

A much less emphasised but fundamental subject in the extant literature is the question of the relevance of the tasks involved in traditional neurocognitive testing. It is unclear how well performance in various neurocognitive tests translates into the functional abilities and mental processes required for competency in the instrumental activities of daily living for older adults. Furthermore, the extent to which exercise-induced cognitive change correlates with (and mitigates) the processes that characterise age-related cognitive decline, is far from established. The notion of ecological validity or the extent to which test outcomes predict real-life behaviour [23], is not reflected in the present literature, but is increasingly being considered in RCTs generally, by the inclusion of a qualitative evaluation aimed at clarifying the everyday relevance and acceptability of study interventions and their intended or unintended outcomes.

A combination or multi-modal exercise intervention that includes motor as well as physical training and requires sustained attention and concentration, may better elicit the actual potency of exercise to enhance cognitive performance, in later life. Conducted as a randomised controlled trial, the study being undertaken will possess the design parameters with the greatest capacity to test the efficacy of such an intervention. Supplementary qualitative data provides greater insight into the clinical, functional and ecological (every-day) relevance of the intervention. In gathering early data into the effects of exercise on cognitive functioning in women (negating the gender effect) and on BDNF levels (as a biomarker of brain plasticity); more robust evidence will have been provided about the mechanisms that link exercise to cognitive improvement. If these questions can be answered future research may be more precisely focused and potentially more productive.

### Aims of the study

The study focuses on women aged 65–75 years, and aims to:

1. test the effect of a complex, multi-modal exercise program on cognitive functions, physical functioning and a biomarker (BDNF) of brain plasticity;

2. explore the associations between changes in cognitive functions and changes in BDNF, over time and;

3. describe the experience of individuals participating in a multi-modal exercise program.

A multi-modal exercise program has been developed by the first author (SV) in consultation with physiotherapists, exercise physiologists and psychologists. The effects of this exercise program are being evaluated in a randomized controlled trial. The theoretical basis of the program incorporates current understandings derived from the literature on ageing, cognitive neuroscience, psychology and exercise science.

## Methods /design

### Study design

The study is a 16-week randomised controlled trial of a multi-modal exercise program for women aged 65–75 years. The study is designed to assess the effect of an exercise intervention combining physical fitness training (aerobic and strength) and motor fitness training (balance, coordination, agility, reaction time and flexibility). Participants are randomly allocated to the intervention group or a no exercise wait list control group (See Figure 1). Measurement of primary and secondary outcomes will take place two weeks prior to commencing the exercise training study (baseline) and within one week of completing the 16 weeks exercise or control period. The protocol has been approved by the Griffith University Human Research Ethics Committee (GU Ref No: PES/05/12/HREC).

**Figure 1 F1:**
[figure not shown]
The design of the study.

### Setting

The study is being conducted in community halls on the Gold Coast which is located in South Eastern Queensland, Australia.

### Study population

The program is designed for non-cognitively impaired, community dwelling older adults. Volunteers are recruited through media coverage, local organisations such as ‘Probus’ and ‘Senior Citizens’ and Government agencies such as the Gold Coast City Council. To be considered for the study, individuals must be:

1. female and aged between 65 and 75 years;

2. doing less than 60 minutes of formal exercise training each week; and

3. able to attend classes twice each week on weekday mornings.

### Eligibility criteria

Exclusion criteria include: a score below 31 on the Telephone Interview of Cognitive Status (TICS) [24]; inability to obtain written clearance from a General Practitioner; a diagnosis of dementia or Parkinson’s disease; the inability to walk 20 meters unaided and head injury within the previous 12 months.

### Informed consent

Informed written consent is obtained before baseline testing takes place.

### Sample size

One hundred participants will be recruited for the study. Sample size is determined using a power calculation to detect between group differences in the primary outcome measures. Previous randomised controlled trials of exercise interventions have shown effect sizes between 0.24 and 1.17, in similar populations, for cognitive performance outcome measures, as a result of aerobic interventions [7]. To obtain 80% statistical power with an α level of 0.05, using a t-test for two independent groups and an effect size of 0.6, the sample size required in each of the two groups is 36 participants (G*Power 3.1) [25,26]. Samples of 50 for both the intervention and control groups are recruited, to allow for attrition.

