### Analyses

The data analysis for the randomised controlled trial will be undertaken on an intention-to-treat basis. To characterize the sample in this study, means or proportions and standard deviations (SDs) will be calculated by randomisation group for multiple baseline demographic, cognitive functioning and anthropometric variables. Unadjusted means and SDs for each cognitive performance measure obtained at the baseline and follow-up visits will be calculated. Missing outcome data will be imputed using multiple imputation [52]. Analysis of covariance will be undertaken for 16 week follow-up outcome measure scores, controlling for baseline cognition (TICS), and using baseline outcome values as covariates. Ninety- five per cent confidence intervals and effect sizes (standardised mean differences) will be calculated for each outcome measure. Differences in follow-up secondary outcome measure scores will be assessed for normality of distribution and either parametric or non-parametric statistical analyses applied as appropriate (e.g. ANCOVA, logistic regression etc.). Hierarchical multiple regression analyses will be used to investigate associations between plasma BDNF levels and a range of independent variables including demographic, anthropometric, cognitive functioning and physical functioning variables.

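### The required 36 per group is reproduced only by an undeclared one-sided t-test; the two-sided test that the protocol implies needs 45, so the attrition margin is 10%, not 28%

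*Protocol article*

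**What the plan says.** The Sample size section of the protocol article sets out a complete calculation. Its purpose is given as follows: "Sample size is determined using a power calculation to detect between group differences in the primary outcome measures". The error rates are "To obtain 80% statistical power with an α level of 0.05", and the method is "using a t-test for two independent groups and an effect size of 0.6". The result is that "the sample size required in each of the two groups is 36 participants (G*Power 3.1"). The section does not say whether the test is one-sided or two-sided. It then adds an allowance: "Samples of 50 for both the intervention and control groups are recruited, to allow for attrition". No attrition rate is given.

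The Analyses section plans a different model from the one used for the sample size: "Analysis of covariance will be undertaken for 16 week follow-up outcome measure scores", adjusted for the Telephone Interview of Cognitive Status score and the baseline value of the outcome. On reporting it says: "Ninety- five per cent confidence intervals and effect sizes (standardised mean differences) will be calculated for each outcome measure".

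**The concern.** All the inputs needed to check the figure are printed except sidedness, and the answer depends heavily on it. The figure of 36 looked too small for a conventional two-sided 0.05 test at an effect of 0.6.

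The rest of the text points to a two-sided test. The stated aim is to detect a difference between groups, without direction. A 95% confidence interval corresponds to a two-sided test at 0.05; a one-sided test at 0.05 would correspond to a 90% interval or a one-sided 95% bound.

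The number matters because 36 is the floor that the attrition allowance protects. If the floor is really 45, most of the apparent room for loss disappears. A trial that ended with 36 to 44 completers per group would believe that it had met its stated t-test power when it had not, and a null result could be read as stronger evidence than it is.

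**Working it through.** **Inputs, from the Sample size section.** Effect size d = 0.6; α = 0.05; target power 80%; t-test for two independent groups; equal groups; 50 recruited per group. Sidedness is not stated, so both cases are computed.

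**Formula.** With n per group, degrees of freedom = 2n − 2 and noncentrality = d × √(n/2). Power is the probability that a noncentral t variable with these parameters exceeds the critical value (upper tail if one-sided, both tails if two-sided). The required n is the smallest that reaches 0.80.

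**Step 1: reproduce the stated 36.** At n = 36, noncentrality = 0.6 × √18 = 2.546 on 70 degrees of freedom.
- One-sided 0.05 (critical value 1.667): power 0.8095. At n = 35 it is 0.7996, just short. The one-sided answer is therefore exactly 36.
- Two-sided 0.05 (critical value 1.994): power 0.709. The figure of 36 is not reproduced.

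**Step 2: the two-sided requirement.**

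| n per group | Noncentrality | Two-sided critical value | Two-sided power |
|---|---|---|---|
| 36 | 2.546 | 1.994 | 0.709 |
| 44 | 2.814 | 1.988 | 0.795 |
| 45 | 2.846 | 1.987 | 0.804 |
| 50 | 3.000 | 1.985 | 0.844 |

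The two-sided answer is 45 per group, or 90 completers. The normal approximation gives 44, so the gap from 36 does not come from the choice of formula. With 36 per group, the effect detectable with 80% two-sided power is about 0.67 instead of 0.60.

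**Step 3: attrition margin.**
- Against 36: 1 − 36/50 = 28%.
- Against 45: 1 − 45/50 = 10%.

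**Step 4: what the planned analysis of covariance could recover.** Adjusting for a baseline value that correlates r with follow-up reduces the residual standard deviation by √(1 − r²), so the effective effect size is approximately 0.6/√(1 − r²). The protocol gives no value of r for these outcomes over 16 weeks; the values below are assumptions. The approximation ignores the small loss of degrees of freedom for the covariates.

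| Assumed r | Effective d | Two-sided power at 36 per group |
|---|---|---|
| 0 | 0.600 | 0.709 |
| 0.3 | 0.629 | 0.749 |
| 0.45 | 0.672 | 0.803 |
| 0.5 | 0.693 | 0.826 |
| 0.7 | 0.840 | 0.940 |

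The break-even correlation for 80% power with 36 completers per group is about 0.45.

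**The case against.** **The figure is right for a one-sided test.** This is true, and two-sidedness is an inference, since the protocol never states it. Some of the text is also directional: the abstract's discussion speaks of improvement in cognitive performance. But the sample-size aim is non-directional, the intervals are 95%, and no one-sided hypothesis is declared. If a one-sided test was intended, the section still omits the one condition needed to obtain 36, and it does not match the planned intervals.

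**The trial will report an analysis of covariance, not a t-test.** This is the strongest objection, and it limits the point. A reader might infer from 70.9% that the reported analysis will miss 80% power. The documents do not support that: if r is about 0.45 or more, 36 per group is enough two-sided. The outcome descriptions cite test-retest reliabilities such as 0.83 to 0.91 for Stroop tests, 0.88 for verbal fluency and 0.70 to 0.80 for letter-number sequencing, so a useful correlation is plausible. These are not 16-week correlations in this population, however, and reaction time has only a split-half figure. Nor does the Sample size section claim any gain from adjustment. The objection therefore removes any claim about the analysis of covariance, but it does not rescue 36 as the answer to the calculation printed.

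**The recruited sample is adequate.** This stands. Two-sided t-test power is 84.4% with 50 per group and stays at or above 80% down to 45. The 28% is also the reviewer's subtraction, not a rate that the protocol states.

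**Conclusion.** The point holds for the required sample size and the attrition margin. From the printed inputs, 36 per group is the answer to a one-sided 0.05 test that the protocol does not declare. On the two-sided reading the requirement is 45 per group, 9 more (25% above the stated figure). At 36 completers per group, the chance of missing a true effect of 0.6 with the unadjusted t-test is about 29% instead of the stated 20%. The loss that can be absorbed at 80% power is 10%, not the implied 28%.

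The conclusion rests on two things: the inference that the test is two-sided, which is well supported but not stated, and the plain t-test that the protocol itself chose for the calculation. It does not extend to the recruitment target of 100, which is adequate if losses are at most 10%, or to the power of the planned analysis of covariance, which depends on a correlation that the document does not give.

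**What to change.** Reword the Sample size paragraph in one of two ways. Neither needs more participants.

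1. **Keep the t-test basis.** State two-sided α 0.05; give the requirement as 45 per group (90 completers); state that 50 per group allows 10% attrition; and note that t-test power falls to about 71% if only 36 per group remain.
2. **Use the planned analysis.** Base the power on the analysis of covariance with two-sided α 0.05. State the assumed baseline/follow-up correlation, justify it for each primary test, and show the range: at 36 per group about 75% at 0.3, 80% at 0.45, 83% at 0.5 and 94% at 0.7. No single value should be called cautious without evidence; 0.5 has no such support in the document, and at 0.3 the figure of 36 falls short.

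If a one-sided test really was intended, say so, justify it, and align the reported intervals with it.

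The cost is one paragraph of text. Under the first option, the stated room for attrition becomes visibly smaller; under the second, the power claim rests openly on an assumption that has to be defended.

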### Randomisation

An automated randomisation service will allocate participants to one of two groups (intervention group or ‘wait-list’ controls). The randomisation service provided by The Clinical Trials Coordinating Centre (CTCC) (Griffith University, Queensland, Australia) is accessed either by telephone or using web-based technology.

### Blinding

Exercise instructors are aware of the allocation of participants; however, all data collectors are blinded to group allocation. Data analysis is conducted by the first author (SV) on a de-identified database.

### Intervention

#### Exercise training intervention

Participants in this group receive a multi-modal exercise class, twice weekly, for a period of 16-weeks. Classes are conducted for 60 minutes and the overall program is designed to include progressions and variations (See Table 1). Each session includes aerobic (cardiovascular), strength (resistance) and motor fitness (balance, co-ordination, flexibility and agility) training in accordance with the ACSM Guidelines for Exercise Testing and Prescription [27] (See Table 2 for details). The cardiovascular component is set to music and choreographed movements are cued in random rather than serial order.

**Table 1 T1:** Overview of three phases of exercise intervention program

**Component**	**Phase 1**	**Phase 2**	**Phase 3**
	**Time**	**Time**	**Time**
**Group freestyle**			
Aerobics	10 mins	15 mins	15 mins
Agility	-	5 mins	5 mins
**Group and/or circuit**			
Strength	15 mins	10 mins	10 mins
Balance	10 mins	10 mins	7 mins
Co-ordination/ Agility/ Reaction time	15 mins	10 mins	7 mins
Cardio	-	-	6 mins
**Group**			
Flexibility and warm down	10 mins	10 mins	10 mins

**Table 2 T2:** Specifics of exercise intervention

**Modality (Type)**	**Format**	**Exercises**	**Examples of exercises**	**Intensity**	**Progressions**	**Variations**
**Phase 1 – Weeks 1-4 – neural adaptation and coordination**						
Cardio (aerobic)	Freestyle aerobics set to music	Antero-postero movements	Marching on the spot	3-4/10 RPE	Increasing number of simultaneous limb movements	Remove lateral movements and shoulder ROM as necessary
		Lateral movements	Three steps forward and back	Music at 124-126 bpm		
		Minimal arm movement				
		Isodirectional upper and lower limb movements	Side step			
			Side tap			
Strength	Group	All major upper, lower body and core muscle groups	Half squats	x2 sets 6-8 reps with light dumbbell (d/b) weights	Commence with no weight progress to light weights (1kg)	Remove weights
			Arm and leg curls			Substitute wrist or ankle weights as necessary.
			Seated theraband rows			
Balance	Group	Static balance with decreasing support as able	Supported standing on one leg	N/A	Increased time + Challenges to concentration	One-to-one supervision and support as necessary
Coordination Agility	Some elements included in free style aerobics	Manoeuvring around and stepping over objects	Weaving in and out of chairs	N/A	Chairs closer	One-to-one supervision and support as necessary
Reaction time	Group	Flat foot heel drumming	Fast, fixed-pattern, foot tapping (seated)			
			Wall ball throws			
Flexibility + warm down	Group	Static stretches on floor	Cat and camel stretches	3-4/10 RPE Minimum 20 secs	Vary with musculo-skeletal status	Substitute as necessary
			Lying hamstring stretches			
			Back extensions			
